**Alternate hypothesis:**

School-based health promotion intervention will decrease the dietary intake of salt (g/day) and sugar (g/day), increase the intake of fruits (g/day) and vegetables (g/day), and decrease the physical inactivity (%) and tobacco and alcohol use (%) among adolescents.

**Methodology**

**Study area**

The study area will be the urban area of **Union Territory of Chandigarh, India.**

Chandigarh is the planned city of the India. The population of the city is 960,787 with the sex ratio of 818 females per 1000 males. Literacy rate of the city is 86.77%. It has 188 schools out of which 115 are government schools and 7 are government aided schools.

| Schools | Government | Recognized private schools |
| --- | --- | --- |
| Nursery School | 1 | ____ |
| Primary Schools | 8 | 4 |
| Middle Schools | 13 | 13 |
| High Schools | 53 | 22 |
| Senior Secondary Schools | 40 | 34 |
| Total schools | 115 | 73 |

***Class wise enrollment of Govt. Schools of Upper Primary Level (Class 8^th^) over the years:***

| **Year** | **Number of students enrolled** |
| --- | --- |
| 2013-2014 | 13,303 |
| 2014-2015 | 14,047 |
| 2015-2016 | 13,776 |
| 2016-1017 | 14,036 |

**Study setting**

Study setting will be schools (government) of Chandigarh UT.

**Population**

The study will be conducted among students, their parents and teachers. As the study focuses mainly on the students and reaches out to their parents & teachers, the study population will be the individuals in the age group of 11-16 yrs for students, their parents & teachers up to age of 65 years.

**Study Design**

Study design is Cluster Randomized Controlled Trial. Each school will be one cluster.

Schools will be randomized to intervention and control group and net changes in the knowledge and practices related to chronic disease risk factors among students, their parents and teachers will be computed by measurements before starting the health promotion intervention and after implementation of the intervention in both intervention and control clusters.

Research approach will be mixed methods: It will have both qualitative & quantitative data. Quantitative data will be collected using validated tools. Qualitative data will be collected by carrying 10 focused group discussions with students, their parents and teachers separately to understand their perception about risk factors and lifestyle behaviors (2 with male teachers, 2 with female teachers, 2 with female students, 2 with male students and 2 with parents in government schools).

**Sample size**

A total of 12 clusters were calculated based on the formula as shown below. Six clusters in intervention arm and six in control arm. As most of the schools in general have strength of 30 students in each section, the size of cluster (m) was taken to be 30 each from a randomly selected section of class 8^th^. Sample size for each indicator (risk factors: Unbalanced diet, physical inactivity, tobacco use and alcohol use) was calculated separately by using data from previous studies.

For quantitative data the sample size will be the same, i.e., 6 clusters in intervention arm & 6 in control arm for students, their parents & teachers in total. For qualitative data the sample size will be max up to 8 participants for each of the focus group discussion.

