**Formula used:**

**c = 1 + f [ π_0_(1 - π_0_)/m + π_1_(1 - π_1_)/m + k^2^ (π_0_^2^ + π_1_^2^) ] / (π_0_ - π_1_)^2^**

Where,

- c is the number of clusters per treatment arm
- f = 7.84 for 5% type I error and 80% power
- π_1_ is the expected proportion in the intervention arm
- π_0_ is the expected proportion in the control arm
- m is the number of individuals in each cluster (assumed equal in all clusters)
- k is the coefficient of variation in the (true) rates or proportions between clusters in each treatment arm

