**Sample size based on the risk factors**

| **Risk Factor** | ***π_0_*** | ***π_1_*** | ***K*** | ***C*** |
| --- | --- | --- | --- | --- |
| Inadequate fruits and vegetable intake^82^ | 0.852 | 0.596 | 0.025 | 12.2 |
| Excess salt intake^83^ | 0.223 | 0.162 | 0.094 | 12.1 |
| Sugar intake (g/day)^84^ | 0.507 | 0.355 | 0.041 | 12.5 |
| Physical inactivity^85^ | 0.232 | 0.162 | 0.099 | 12.1 |
| Tobacco use^85^ | 0.049 | 0.034 | 0.163 | 11.4 |
| Alcohol use^86^ | 0.345 | 0.242 | 0.057 | 12.4 |
| Total clusters selected: Twelve | | | | |

Schools will be selected randomly for control and intervention groups (based on the consent) from the list of randomly selected schools.

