***Adolescents***

A number will be assigned on folded paper slips for all the sections of the 8^th^ grade. Later, a slip will be randomly selected from the shuffled lot by a person other than the researcher. The section numbered in the slip will be then be selected as the cluster for the study. The above-mentioned method will be applied to select a section of 8^th^ grade in each of the selected twelve schools. Adolescents studying in 8^th^ grade are between 10-16 years of age. All students from class who give the consent to be part of the research study will be involved in the study.

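### A per-arm cluster number is used as the trial total: with six schools per arm, five of the six indicators miss the 80% power behind the sample size

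*Protocol*

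**What the plan says.** The Protocol's list under Formula used defines the quantity being computed: "c is the number of clusters per treatment arm". The same list sets the error rates: "f = 7.84 for 5% type I error and 80% power".

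The table under Sample size based on the risk factors gives C = 12.2 (inadequate fruit and vegetable intake), 12.1 (salt), 12.5 (sugar), 12.1 (physical inactivity), 11.4 (tobacco) and 12.4 (alcohol). Its last line reads "Total clusters selected: Twelve".

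The Sample size section reports the same number as a total and then splits it: "A total of 12 clusters were calculated based on the formula as shown below. Six clusters in intervention arm and six in control arm". Cluster size m is set at 30, a full section of class 8. Under Sampling Framework, the Schools paragraph repeats twelve as the number of schools required, and the Adolescents paragraph limits entry: "All students from class who give the consent to be part of the research study will be involved in the study".

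**The concern.** A number that the formula defines for one arm has been spent on both arms. Nothing in the protocol says that C in the table was already doubled, or gives another reason for six schools per arm.

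The protocol says that the size was calculated separately for each risk factor, and its hypotheses name all of these behaviours. A null result on any of them would therefore be read as coming from a trial with 80% power. If the actual power is well below that, such a result says little about whether the intervention works.

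**Working it through.** **Inputs.** π0, π1 and k come from the table of risk factors, m = 30 from Sample size, and f = 7.84 from Formula used. The last is (1.96 + 0.84)², that is, two-sided 5% and 80% power.

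**Formula.** c = 1 + f·V/(π0 − π1)², with V = π0(1 − π0)/m + π1(1 − π1)/m + k²(π0² + π1²).

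**Step 1: reproduce the printed C.** For sugar, V = 0.507 × 0.493/30 + 0.355 × 0.645/30 + 0.041² × (0.507² + 0.355²) = 0.00833 + 0.00763 + 0.00064 = 0.01661. The squared difference is 0.152² = 0.02310. So c = 1 + 7.84 × 0.01661/0.02310 = 6.6 per arm, against 12.5 printed. All rows are in the table below. Only alcohol comes close, and it does so as a per-arm figure.

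**Step 2: could the printed C be a total?** Then 2c should match it. It does not: only sugar is near (13.3 against 12.5). Dropping the leading 1, leaving k unsquared, or using f for 90% power or a one-sided test does not reproduce the column either. The m needed to obtain each printed C runs from about 4 to 390. For salt, inactivity and tobacco no k of zero or more gives the printed value at m = 30.

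**Step 3: power with six per arm.** Inverting the formula, power = Φ(√[(c − 1)(π0 − π1)²/V] − 1.96) with c = 6. For sugar: √(5 × 0.02310/0.01661) = 2.637, and Φ(0.677) = 75%.

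| Indicator | π0, π1, k | Printed C | c per arm | 2c | Power, 6 per arm | Power, 12 per arm |
|---|---|---|---|---|---|---|
| Fruit/vegetables | 0.852, 0.596, 0.025 | 12.2 | 2.5 | 5.1 | >99% | >99% |
| Sugar | 0.507, 0.355, 0.041 | 12.5 | 6.6 | 13.3 | 75% | 97% |
| Alcohol | 0.345, 0.242, 0.057 | 12.4 | 11.5 | 23.0 | 49% | 82% |
| Inactivity | 0.232, 0.162, 0.099 | 12.1 | 19.0 | 38.0 | 31% | 59% |
| Salt | 0.223, 0.162, 0.094 | 12.1 | 24.1 | 48.2 | 26% | 49% |
| Tobacco | 0.049, 0.034, 0.163 | 11.4 | 96.6 | 193.1 | 9% | 16% |

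A noncentral t calculation on cluster summaries (10 degrees of freedom) gives >99%, 74%, 48%, 31%, 25% and 9% for six per arm, in the same order.

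**Step 4: smallest difference detectable at 80% power.** Solving c = 6 for π1 at m = 30 gives, in percentage points (planned difference in brackets): fruit/vegetables 13.6 (25.6), sugar 16.1 (15.2), alcohol 14.5 (10.3), inactivity 12.4 (7.0) and salt 12.1 (6.1). For tobacco there is no solution. Even π1 = 0 needs c = 1 + 7.84 × [0.049 × 0.951/30 + 0.163² × 0.049²]/0.049² = 6.3.

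**Step 5: smaller clusters.** The protocol gives no rate of refusal or loss, so these values of m are assumptions. Sugar power with six per arm is 71% at m = 27, 66% at m = 24 and 58% at m = 20. At m = 24, fruit/vegetables stays above 99% and salt falls to 22%.

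**The case against.** The strongest reply is that the shortfall is not uniform and that the printed column is a poor guide to it. That stands. On the tabled inputs fruit and vegetable intake is comfortably powered with six schools per arm, and sugar is only slightly short.

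Three stronger readings are tempting, and the protocol does not support them.

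- **Power is 46% to 49% for every indicator.** This follows if each printed C is accepted as the per-arm requirement: Φ(√(7.84 × 5/(C − 1)) − 1.96) is 49% at C = 11.4 and 46% at C = 12.5. But the column does not reproduce from its inputs. The figure is roughly right for alcohol only. It is too low for fruit/vegetables and sugar, and too high for inactivity, salt and tobacco.
- **The trial has half the schools it needs, so 24 to 26 would cure it.** Twelve per arm reaches 80% for fruit/vegetables, sugar and alcohol only. Covering tobacco would take 97 per arm, or 194 schools, against 115 public schools on the list.
- **The 80% is lost everywhere.** It is lost for five of the six indicators.

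The point about consent is secondary, because its size depends on a rate that the protocol does not give.

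**Conclusion.** The contradiction stands: the formula defines c per arm, while the Sample size section, the last line of the table and the Schools paragraph use it as the total. With six schools per arm the 80% power behind the design is not delivered for five of the six indicators. Power is 75% for sugar, 49% for alcohol, 31% for inactivity, 26% for salt and 9% for tobacco; fruit/vegetables exceeds 99%.

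These figures rest on the protocol's own π0, π1, k, f and m = 30, with equal cluster sizes and every enrolled student measured. Fewer students per cluster would lower them. They apply to the proportions in the table. The hypotheses express salt, sugar, fruit and vegetables in g/day, and this calculation does not cover those scales.

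**What to change.** 1. In Sample size, in the closing line of the risk-factor table and in the Schools paragraph under Sampling Framework, use c as a per-arm number, in agreement with Formula used.
2. Recompute the C column from the stated π0, π1, k and m, or correct the inputs if those are what is misprinted.
3. If six plus six schools is kept, drop 80% power as the basis for the size. State instead, for each indicator, the power obtained and the smallest difference detectable at 80% power (steps 3 and 4), and say that no reduction in tobacco use is detectable at that power.
4. Show these figures over a range of m below 30, since only consenting students enter and no loss is allowed for.

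The cost is a revised text and table and a less favourable stated power. No extra schools are needed.

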**Statistical Analysis**

Descriptive statistics such as mean, standard deviation, student’s t-test, will be done separately for both the sexes. Chi-square test will be done for categorical variables. Change in various indicators will be computed in intervention and controls. Multivariable regression will be done to measure the effect of intervention after controlling for the confounding variables, if any. All the statistical analysis will be done using Statistical Package for Social Sciences (SPSS) or R.

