**Ethical Considerations**

Permission for conducting the study is taken from Institute’s Ethical Committee (INT/IEC/2018/000082; Date: 22/ 01/2019) and the study is registered under the Clinical Trial Registry of India (CTRI/2019/09/021452; 30/09/2019). During this study the participant’s data will be kept confidential. This study will not cause any harm to participants and they can refuse to participate in the study at any time.

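### The sample size takes m = 30 from the usual class roll, with no allowance for pupils who decline or are lost, so unless sections exceed 30 the stated size and power are too favourable

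*Protocol*

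**What the plan says.** The Sample size section derives m from the class roll: "As most of the schools in general have strength of 30 students in each section, the size of cluster (m) was taken to be 30". Under Formula used, that value enters with this definition: "m is the number of individuals in each cluster (assumed equal in all clusters". The design is fixed as "Six clusters in intervention arm and six in control arm", and the target is "f = 7.84 for 5% type I error and 80% power".

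Other sections determine how many pupils are actually observed:

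- **Sampling Framework, Adolescents.** One class-8 section is drawn by lot in each of the twelve schools. Entry is by consent: "All students from class who give the consent to be part of the research study will be involved in the study". No second section and no replacement of pupils is described.
- **Ethical Considerations.** Participants are told "they can refuse to participate in the study at any time".
- **Objectives, Study Design and Methods for Objective 3.** The intervention lasts six months, and the effect is judged from a baseline and an endline survey.
- **Statistical Analysis.** "Change in various indicators will be computed in intervention and controls".

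The protocol does provide for refusal by schools: it lists 24 in order to secure 12. It has no matching provision for pupils, in either m or the number of clusters.

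**The concern.** The roll is the number of pupils approached. The formula's m is the number whose outcomes form each school's proportion at endline. Using the first for the second leaves no margin for a pupil who declines, withdraws or is absent at endline.

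This matters because the between-school coefficients of variation in the table are small (0.025 to 0.163). The pupil-level part of the variance therefore dominates, and the required number of clusters rises almost in proportion to 1/m.

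The same calculation has two separate faults: the C column does not follow from the formula, and about 12 is used as the total although "c is the number of clusters per treatment arm". If both are corrected and m stays at 30, the restated size will still be too favourable. The basis of m is set in this protocol, so it is not a detail left to a statistical analysis plan.

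**Working it through.** **Inputs.** π0, π1 and k come from the table under Sample size based on the risk factors. f = 7.84 and m = 30 come from the protocol. The loss rate is an assumption, because the protocol gives none: 10%, 20% and 30%, so m = 30 × (1 − loss) = 27, 24, 21. Over 12 schools that is 324, 288 or 252 pupils instead of 360.

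**Formulas.**

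- V = π0(1 − π0)/m + π1(1 − π1)/m + k²(π0² + π1²)
- Clusters per arm: c = 1 + 7.84 V/(π0 − π1)²
- Power with six schools per arm (the same formula inverted): Φ(√[5(π0 − π1)²/V] − 1.96)

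**Step 1: the plan's own figures.** For sugar at m = 30:

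- Pupil-level term: (0.507 × 0.493 + 0.355 × 0.645)/30 = 0.01596
- Between-school term: 0.041² × (0.507² + 0.355²) = 0.00064
- V = 0.01661 and (π0 − π1)² = 0.02310, so c = 1 + 7.84 × 0.01661/0.02310 = 6.6. The table states 12.5.

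The other rows do not reproduce either (see the table below). The m that would return each stated C runs from 3.9 (fruit and vegetables) to 389 (tobacco). No single m explains the column, so the stated values do not hide an allowance for lost pupils.

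**Step 2: weight of m.** At m = 30 the pupil-level term is 93% to 97% of V in every row (sugar: 0.01596/0.01661 = 96%).

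**Step 3: sugar with a 20% loss.** The pupil-level term becomes 0.47893/24 = 0.01996, so V = 0.02060 and c = 1 + 7.84 × 0.02060/0.02310 = 8.0. Power = Φ(√[5 × 0.02310/0.02060] − 1.96) = Φ(0.41) = 66%, against 75% at m = 30.

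**Step 4: all rows.**

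| Risk factor | Stated C | c per arm at m = 30 / 27 / 24 / 21 | Power (%), six per arm, at m = 30 / 27 / 24 / 21 |
| --- | --- | --- | --- |
| Fruit and vegetables | 12.2 | 2.5 / 2.7 / 2.9 / 3.2 | 99.9 / 99.8 / 99.5 / 98.9 |
| Salt | 12.1 | 24.1 / 26.5 / 29.5 / 33.4 | 25.5 / 23.6 / 21.5 / 19.5 |
| Sugar | 12.5 | 6.6 / 7.2 / 8.0 / 9.0 | 75.1 / 70.8 / 65.8 / 60.2 |
| Physical inactivity | 12.1 | 19.0 / 20.9 / 23.2 / 26.2 | 31.4 / 28.9 / 26.4 / 23.8 |
| Tobacco | 11.4 | 96.6 / 106.8 / 119.6 / 136.1 | 9.4 / 8.8 / 8.3 / 7.8 |
| Alcohol | 12.4 | 11.5 / 12.6 / 14.0 / 15.8 | 48.8 / 45.1 / 41.1 / 36.9 |

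A 10% loss raises the required c by about 7% to 11%, and a 20% loss by about 15% to 24%.

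**Step 5: roll needed to keep 30 analysed.** 30/0.9 = 33.3, 30/0.8 = 37.5 and 30/0.7 = 42.9, so rolls of 34, 38 and 43.

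**The case against.** **Thirty is a typical roll, not a cap.** The protocol speaks of most schools in general, sets no maximum per section, and gives no roll for any drawn section. A reader might infer that 30 analysed pupils cannot be reached once anyone declines, or that it needs full consent and full retention in all twelve schools. The text does not support that, because a larger section would absorb some loss. What remains is that the plan states no such margin, and its formula assumes equal clusters of 30.

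**Paired data are not required.** A reader might also infer from the Statistical Analysis section that only pupils with both surveys count. It says only that change will be computed in the two groups, which can be done at arm or school level, and the formula has no baseline term. The point therefore concerns pupils analysed at endline, not complete pairs.

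**The loss is assumed.** The right to refuse is a general ethical statement and does not predict a rate. This stands, so the figures above are a range and not a forecast.

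**The effect is small next to the other faults.** With six schools per arm, five of the six indicators are already below 80% power at m = 30. The sixth stays near 99%, so loss moves no row across 80%. This also stands. It would matter more if the trial were restated at twelve per arm: alcohol would have 82% power at m = 30, but 78%, 73% and 67% at m = 27, 24 and 21.

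**Conclusion.** The point holds in a conditional form. m = 30 is the usual number approached per section, and the protocol uses it as the number analysed with no margin for refusal, withdrawal or absence at endline. Where rolls do not exceed 30 by enough to cover the loss, the size and the 80% power are overstated.

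Across the assumed 10% to 30% range, the largest cost in power with six schools per arm is for sugar, about 4 to 15 percentage points. For alcohol it is about 4 to 12 points, and for fruit and vegetables about 1 point at most. These figures rest on the protocol's own proportions and k, equal cluster sizes, the normal approximation built into its formula, and a loss rate that it does not give.

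This is a secondary input to a calculation that must be redone anyway. It does not by itself change which indicators reach 80% power under the planned six schools per arm.

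**What to change.** In the Sample size section:

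1. Define m as the expected number of pupils per school analysed at endline: section roll × expected consent × expected retention. State the assumed rates and their basis, or show a range if there is none.
2. Label 30 as the number approached per section.
3. Use this m when the clusters per arm and the power with six schools per arm are recalculated and restated, together with correction of the C column and of the use of 12 as a total.

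The cost is wording and one recalculation. No added pupils are required, and the stated power becomes less favourable. Recovering the lost power, as opposed to stating it correctly, would be a separate decision needing more schools or more than one section per school.

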**Formula used:**

**c = 1 + f [ π_0_(1 - π_0_)/m + π_1_(1 - π_1_)/m + k^2^ (π_0_^2^ + π_1_^2^) ] / (π_0_ - π_1_)^2^**

Where,

- c is the number of clusters per treatment arm
- f = 7.84 for 5% type I error and 80% power
- π_1_ is the expected proportion in the intervention arm
- π_0_ is the expected proportion in the control arm
- m is the number of individuals in each cluster (assumed equal in all clusters)
- k is the coefficient of variation in the (true) rates or proportions between clusters in each treatment arm

**Sample size based on the risk factors**

| **Risk Factor** | ***π_0_*** | ***π_1_*** | ***K*** | ***C*** |
| --- | --- | --- | --- | --- |
| Inadequate fruits and vegetable intake^82^ | 0.852 | 0.596 | 0.025 | 12.2 |
| Excess salt intake^83^ | 0.223 | 0.162 | 0.094 | 12.1 |
| Sugar intake (g/day)^84^ | 0.507 | 0.355 | 0.041 | 12.5 |
| Physical inactivity^85^ | 0.232 | 0.162 | 0.099 | 12.1 |
| Tobacco use^85^ | 0.049 | 0.034 | 0.163 | 11.4 |
| Alcohol use^86^ | 0.345 | 0.242 | 0.057 | 12.4 |
| Total clusters selected: Twelve | | | | |

Schools will be selected randomly for control and intervention groups (based on the consent) from the list of randomly selected schools.

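### The salt row of the sample-size table breaks the pattern of the other five rows and needs checking; separately, its printed cluster number follows from no candidate pair of rates

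*Protocol*

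**What the plan says.** Under Sample size, the protocol says that each risk factor was sized separately from earlier studies. It arrives at twelve clusters, six per arm, and "the size of cluster (m) was taken to be 30 each from a randomly selected section of class 8^th". The formula section defines c as the number of clusters in each arm and sets "f = 7.84 for 5% type I error and 80% power".

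The table headed Sample size based on the risk factors has six rows. Its columns are, in order, the control rate π0, the intervention rate π1, the between-cluster coefficient of variation k, and C. The salt row reads "Excess salt intake^83^ | 0.223 | 0.162 | 0.094 | 12.1". Two rows further down, after sugar, the table gives "Physical inactivity^85^ | 0.232 | 0.162 | 0.099 | 12.1". The rates in the remaining four rows are set out in the check below; their k values are 0.025 for fruit and vegetables, 0.041 for sugar, 0.163 for tobacco and 0.057 for alcohol.

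The table closes with a total of twelve clusters. The protocol gives no rule by which π1 was obtained from π0.

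**The concern.** Salt and physical inactivity share the same π1, 0.162, although their control rates differ. Salt is also the one row whose relative reduction departs from about 30%. Together these suggest that one salt cell was miscopied: either π1 was carried across from the inactivity row, or the digits of π0 were swapped.

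Salt intake is the first outcome named in the hypotheses, and sodium estimated from spot urine is the only biochemical measure of effect in Objective 3. Its planning inputs should therefore be traceable. If the sponsor repaired only the C column and left this pair unverified, the new salt figure could rest on an effect size that nobody intended.

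A second matter concerns the same row: whether its printed C can be obtained from the protocol's formula at all.

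**Working it through.** **Step 1. Ratio check.** Multiply each π0 by 0.7 and compare with the printed π1.

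| Row | π0 | 0.7 × π0 | π1 printed | 1 − π1/π0 |
|---|---|---|---|---|
| Fruit and vegetables | 0.852 | 0.5964 | 0.596 | 30.0% |
| Salt | 0.223 | 0.1561 | 0.162 | 27.4% |
| Sugar | 0.507 | 0.3549 | 0.355 | 30.0% |
| Physical inactivity | 0.232 | 0.1624 | 0.162 | 30.2% |
| Tobacco | 0.049 | 0.0343 | 0.034 | 30.6% |
| Alcohol | 0.345 | 0.2415 | 0.242 | 29.9% |

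Five rows agree to three decimals and salt does not. The five agreeing rates cite four different references (82, 84, 85 and 86), so a common ratio of 0.70 points to a planning convention rather than to five separately sourced values of π1.

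**Step 2. Try to reproduce the printed salt C of 12.1.** Formula: c = 1 + f × V / (π0 − π1)², where V = π0(1 − π0)/m + π1(1 − π1)/m + k²(π0² + π1²). Inputs are f = 7.84, m = 30 and the salt k = 0.094.

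- Printed pair 0.223/0.162: V = 0.005776 + 0.004525 + 0.000671 = 0.010972; squared difference 0.003721; c = 1 + 23.1 = **24.1 per arm**.
- Pair 0.223/0.156 (π1 changed): V = 0.005776 + 0.004389 + 0.000654 = 0.010819; squared difference 0.004489; c = 1 + 18.9 = **19.9 per arm**.
- Pair 0.232/0.162 (π0 changed): V = 0.005939 + 0.004525 + 0.000707 = 0.011172; squared difference 0.004900; c = 1 + 17.9 = **18.9 per arm**.

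None gives 12.1, whether read per arm or as a total (a total doubles each figure; the printed pair gives 48.2). Variants on the printed pair also fail:

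| Variant | c |
|---|---|
| Without the added 1 | 23.1 |
| k not squared | 37.8 |
| k = 0 | 22.7 |
| One-sided f = 6.18 | 19.2 |
| 90% power, f = 10.5 | 32.0 |
| m = 60 | 13.3 |

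To obtain 12.1 per arm with π0 = 0.223 and m = 30, π1 would have to be about 0.138.

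**Step 3. Power at the planned size.** Inverting the same formula, power = Φ(|π0 − π1| × √((c − 1)/V) − 1.96).

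| Salt pair | 6 schools per arm | 12 schools per arm |
|---|---|---|
| 0.223/0.162 | Φ(1.302 − 1.96) = 26% | Φ(1.931 − 1.96) = 49% |
| 0.223/0.156 | Φ(1.440 − 1.96) = 30% | Φ(2.136 − 1.96) = 57% |
| 0.232/0.162 | Φ(1.481 − 1.96) = 32% | Φ(2.197 − 1.96) = 59% |

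**Step 4. Is the mismatch confined to salt?** Applying the formula to the other rows as printed, c per arm against printed C is: fruit and vegetables 2.5 against 12.2, sugar 6.6 against 12.5, inactivity 19.0 against 12.1, tobacco 96.6 against 11.4, and alcohol 11.5 against 12.4. No row reproduces, so the failure in Step 2 belongs to the whole column and is not produced by the 0.162.

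**The case against.** The strongest reply is that nothing here proves an error. The protocol says that each indicator was sized separately from earlier studies, which leaves room for a salt-specific effect, and no 30% rule is written down. That stands. The duplicated value and the swapped digits make a slip likely, but whether one occurred, and in which cell, can be settled only from reference 83 and the sponsor's own planning notes. If salt did have its own effect size, the protocol does not say why, so a sentence would still be needed.

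Three stronger readings are tempting and should be resisted. A reader might infer that the salt pair is simply wrong; the documents show an unexplained departure, not a demonstrated error. A reader might infer that 0.162 is why the salt requirement is misstated; it is not, since 12.1 follows from none of the three pairs and the other rows fail as well. And because the printed pair yields more clusters than either alternative, a reader might infer that the protocol oversized salt. The figure of 24.1 is a recomputation and appears nowhere in the protocol; the 12.1 that does appear lies below all three recomputed values.

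It can also be said that little turns on the choice. The suspected slip runs in the conservative direction, towards a smaller effect; power at six schools per arm differs by only about six percentage points across the pairs; and the hypotheses state salt in grams per day, whereas this row sizes a proportion. All of that is fair and limits the weight of the point. It does not remove the need for a traceable input and a requirement that agrees with the formula.

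**Conclusion.** The point holds as an inconsistency to be explained or corrected. Salt alone departs from π1 = 0.7 × π0, with a 27.4% reduction against 29.9% to 30.6% elsewhere, and its π1 matches the row whose π0 is the salt π0 with two digits swapped. That a common 30% reduction was intended is an inference from five rows.

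Separately, the salt C of 12.1 is not obtainable from the stated formula: the three candidate pairs need 24.1, 19.9 or 18.9 clusters per arm. At six schools per arm the formula gives about 26%, 30% or 32% power, against the 80% built into f. These figures assume 30 pupils analysed in every cluster and the printed salt k of 0.094, which is kept for all three pairs. The choice of pair shifts the numbers modestly; the conclusion that salt is far short of 80% does not depend on it. This is secondary to the failure of the whole C column and to the use of a per-arm c as a total of twelve, and is best handled with them.

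**What to change.** 1. Check the salt π0 and π1 against reference 83 and the planning records. Correct whichever cell is wrong, or add a sentence saying why salt has its own effect size.
2. State a common 30% relative reduction in the text only if that was the rule used.
3. From the verified pair, restate the salt requirement and the power at six schools per arm. Do this while recomputing the whole C column, and settle whether C counts clusters per arm, as the formula section defines c, or the total of twelve, as the table and the six-per-arm allocation treat it.

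The cost is at most one corrected cell, a sentence or two, and a recomputed table. Enrolment need not change. The downside is that the protocol will then show a salt power well below 80%.

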**HYPOTHESIS**

**Null hypothesis:**

School-based health promotion intervention will not lead to any change in the dietary intake of salt (g/day), sugar (g/day), fruits (g/day), vegetables (g/day), physical inactivity (%), tobacco and alcohol use (%) among adolescents.

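### The four diet hypotheses are stated in g/day but the sample size treats diet as proportions, so the power for salt, sugar, fruits and vegetables is not established

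*Protocol*

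**What the plan says.** The Null hypothesis section names seven outcomes on two scales: "dietary intake of salt (g/day), sugar (g/day), fruits (g/day), vegetables (g/day), physical inactivity (%), tobacco and alcohol use (%) among adolescents". The Alternate hypothesis keeps the same scales and adds directions: the intervention "will decrease the dietary intake of salt (g/day) and sugar (g/day), increase the intake of fruits (g/day) and vegetables (g/day"). Fruits and vegetables are separate outcomes.

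Under Formula used, the effect is defined only through proportions. For example, "π_1_ is the expected proportion in the intervention arm", and the control-arm term is defined likewise. The error basis is "f = 7.84 for 5% type I error and 80% power".

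The table under Sample size based on the risk factors has three diet rows:

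- a row for excess salt intake, with 0.223 against 0.162;
- "Inadequate fruits and vegetable intake^82^ | 0.852 | 0.596 | 0.025 | 12.2", one row for two hypotheses;
- "Sugar intake (g/day)^84^ | 0.507 | 0.355 | 0.041 | 12.5".

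The Statistical Analysis section plans means, standard deviations and t-tests, and keeps the chi-square test for categorical variables.

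**The concern.** A power statement belongs to a particular outcome on a particular scale. Here the hypotheses to be tested and the outcomes used to size the trial differ in scale for all four diet outcomes, and in number for fruits and vegetables. The protocol gives no mean, SD or target difference in g/day. It also gives no cut-off for excess or inadequate intake, so the table's outcomes cannot be rebuilt from g/day data either.

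Two things are at stake. A reader cannot tell what change in grams twelve schools could detect. And each diet outcome exists in two versions, a g/day intake and an undefined split, which leaves room to choose between them after the data are seen.

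**Working it through.** **1. Match hypotheses to sample size rows.**

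| Hypothesised outcome | Scale in hypotheses | Row in sample size table | Same scale? |
|---|---|---|---|
| Salt | g/day | proportion with excess intake | no |
| Sugar | g/day | labelled g/day, entries used as proportions | no |
| Fruits | g/day | combined proportion | no |
| Vegetables | g/day | same combined row | no |
| Physical inactivity | % | proportion | yes |
| Tobacco | % | proportion | yes |
| Alcohol | % | proportion | yes |

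Four of seven do not match. The Sample size section's remark that the quantitative part uses the same clusters only sets the survey apart from the focus groups; it is not a calculation for continuous outcomes.

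**2. Try to reproduce the plan's own figures.** The protocol's formula is c = 1 + 7.84 × V / (π0 − π1)², with V = π0(1 − π0)/m + π1(1 − π1)/m + k²(π0² + π1²), m = 30, and c defined as clusters per arm.

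- Sugar: V = 0.00833 + 0.00763 + 0.00064 = 0.01661; c = 1 + 7.84 × 0.01661 / 0.152² = 6.64.
- Salt: V = 0.00578 + 0.00453 + 0.00067 = 0.01097; c = 1 + 7.84 × 0.01097 / 0.061² = 24.12.

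| Row | c per arm, recomputed | twice that | stated C |
|---|---|---|---|
| Fruit and vegetables | 2.54 | 5.09 | 12.2 |
| Salt | 24.12 | 48.24 | 12.1 |
| Sugar | 6.64 | 13.27 | 12.5 |
| Inactivity | 19.00 | 38.00 | 12.1 |
| Tobacco | 96.56 | 193.1 | 11.4 |
| Alcohol | 11.51 | 23.02 | 12.4 |

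No single reading gives the column. Alcohol comes near as a per-arm figure and sugar as a two-arm total. In addition, a C of about 12, defined per arm, is used as the total (6 + 6).

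**3. What can be said on the g/day scale.** Nothing in grams, because no mean, SD or between-school variation in g/day is given. In SD units, with 6 schools of 30 per arm (180 pupils) and an assumed intracluster correlation (ICC), d = (1.96 + 0.84) × √[2(1 + 29 × ICC)/180].

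| Assumed ICC | 0 | 0.01 | 0.02 | 0.05 | 0.10 |
|---|---|---|---|---|---|
| Detectable difference (SD) | 0.30 | 0.34 | 0.37 | 0.46 | 0.58 |

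This is a normal approximation. With a t reference on 10 degrees of freedom the range is 0.33 to 0.65 SD. Keeping the formula's added cluster (5 in place of 6, a factor √(6/5) = 1.095) gives almost the same, 0.32 to 0.64 SD.

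**The case against.** The best defence is that the mismatch may be harmless. A comparison of means usually carries more information than a comparison of split data, so a trial sized on proportions could have ample power in g/day. The sugar label may be a slip, since the formula defines both terms as proportions. The word mean does not appear in the hypotheses; it is inferred from the units and the planned t-tests. Much of this stands, and it rules out some stronger readings.

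- **A reader might infer that power for the diet outcomes is below 80%.** The documents do not show that. Suppose each intake were normal with equal SD in both arms and the table's proportions came from a single cut-off. The shifts would then be z(π0) − z(π1): 0.80 SD for the combined fruit and vegetable row, 0.39 for sugar and 0.22 for salt. Against 0.30 to 0.58 SD, the first is detectable throughout, the second depends on the ICC, and the third is not. These assumptions are not in the protocol, and it names no g/day target, so the answer is open in both directions.
- **A reader might infer that the 80% basis misses every hypothesis.** On scale it misses only the four diet outcomes.
- **A reader might infer a loss of efficiency from dichotomising.** For independent, normal data, φ(z)²/[p(1 − p)] at the table's control rates is 0.64 (sugar), 0.51 (salt) and 0.42 (fruit and vegetables), or 1.6 to 2.4 times as many pupils. This is an upper end that ignores clustering. If the ICC of the split outcome is taken as efficiency times the continuous ICC, the ratios fall to 1.23, 1.39 and 1.56 at a continuous ICC of 0.05. Nor does the protocol plan to dichotomise; its t-tests point the other way.

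What the defence does not supply is a calculation for any g/day outcome.

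**Conclusion.** The concern holds in this limited form. For salt, sugar, fruits and vegetables, four of seven hypothesised outcomes, the stated error and power basis refers to different outcomes from those in the hypotheses. Their power is therefore unestablished. The contradiction lies between two parts of the protocol that are both written out, so it is not a detail that a separate analysis plan would be expected to supply. The 0.30 to 0.58 SD range is for orientation only: it rests on assumed ICCs, equal clusters of 30 and a normal approximation, and it cannot be turned into grams without an SD.

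The failure of the cluster column to follow from its inputs is a separate fault. Because of it, correcting the scale of the diet rows would not by itself give a valid power statement for inactivity, tobacco and alcohol. By the protocol's own inputs, Φ(|π0 − π1|/√(V/6) − 1.96) gives about 37%, 10% and 56% for these at 6 schools per arm, without the formula's added cluster.

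**What to change.** 1. Keep g/day as the tested scale for the four diet outcomes, in line with the planned t-tests.
2. Replace the three diet rows by four, with fruits and vegetables apart, using the means version of the same formula: c = 1 + f[(s0² + s1²)/m + k²(μ0² + μ1²)]/(μ0 − μ1)², where s is the within-school SD and k the between-school coefficient of variation, both on the g/day scale.
3. Take s and k (or an ICC) from the cited sources, if they report them, or from the planned baseline survey, pooled and blind to arm. Twelve schools estimate between-school variation poorly, so show a range.
4. State the detectable g/day difference for each outcome at 6 schools of 30 per arm.
5. Correct the sugar label, and report the proportions as secondary outcomes with defined cut-offs.
6. Separately, recompute the cluster column from its inputs and settle whether C is per arm or in total.

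Restating the diet hypotheses as proportions with defined cut-offs would also remove the contradiction, but it discards information.

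Items 1 to 5 cost a recalculation and protocol wording. They need no extra pupils only because the trial is held at its present size and reports what that size can detect; whether that difference is small enough to be useful remains to be judged.
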